## Abstract

**Background:**

The worldwide prevalence of anxiety in older adults is estimated at between 6 and 10%. In Canada, adults 65 and older experience anxiety at a rate of 6.4%, affecting more than 300,000 people. Anxiety in older adults has been linked to difficulties retaining new information and engaging in instrumental daily activities of living. Due to COVID-19 restrictions, novel methods of delivering therapy programs remotely are needed; however, data is limited. There is some evidence that older adults prefer non-pharmacological approaches for anxiety that can be delivered in the community. Emotion-focused mindfulness therapy (EFMT) is a mindfulness-based intervention that emphasizes meditation and observing thoughts and emotions as they arise. This emphasis has been demonstrated to reduce symptoms of anxiety in general populations. This study aims to evaluate the feasibility of EFMT with older adults.

**Methods:**

This pilot feasibility randomized controlled trial will use a wait list control trial design. Due to COVID-19 restrictions, we will use telehealth delivery via Zoom rather than in-person delivery. The first 48 people to meet the eligibility criteria will be randomly allocated to either receive EFMT immediately, or in approximately 8 weeks time from enrollment (1:1 allocation ratio). Data will be collected at baseline, 8 weeks following baseline, and 16 weeks following baseline. The primary outcomes will determine the feasibility of the intervention based on recruitment, enrolment, retention, and adherence to all components of the intervention. The secondary outcome will be changes to anxiety over time.

**Discussion:**

The results of this trial will determine the feasibility and potential effectiveness of video-delivered EFMT for late-life anxiety compared to no treatment. If the results are promising, a larger randomized controlled trial may be conducted.

**Trial registration:**

ClinicalTrials.gov, NCT04415528. Registered on June 4, 2020

**Protocol version:**

Protocol version 2, January 2, 2021

**Supplementary Information:**

The online version contains supplementary material available at 10.1186/s40814-021-00905-0.

## Introduction

### Background and rationale

The worldwide prevalence of anxiety in older adults is estimated at between 6 and 10% [1, 2]. However, actual numbers may be higher because anxiety frequently goes undiagnosed in adults 65 and older, although symptoms such as insomnia, irritability and agitation are reported to primary care providers [3]. This high prevalence of anxiety is of concern because anxiety is linked to decline in memory and is a leading cause of disability in older adults [4–7]. In a study of 79 older adults, those with anxiety showed a greater decline in memory over a 4-year period [5]. The worldwide prevalence of cognitive impairments has been estimated at between 10 and 20% in people over 65 [8–13]. Mild cognitive impairment (MCI) can be understandably troubling for those living with the condition because MCI may be a prodromal symptom of dementia, with up to 15% of people progressing to dementia [14].

Anxiety in older adults has also been linked to negative effects on quality of life, problems managing stress, difficulty retaining new information, and sleep disturbances [15–17]. Older adults who self-report anxiety, depression, or both also experience a decline in functional activities, difficulties with the instrumental activities of daily living, increased mortality due to illness, suicidal ideation particularly among men, and increased use of health care services [3, 18]. Present treatments for anxiety in adults 55 and older have met with limited success. While pharmacotherapy is frequently used to manage symptoms of anxiety in older adults, this approach has been related to negative side effects such as cardiovascular issues and falls [3, 19–22]. There is evidence in the research literature to suggest that older adults favor non-pharmacotherapy approaches, such as psychotherapy, but do not always have access to public mental health care, or can afford private mental health care [3, 23]. Given the increased rates of anxiety due to COVID-19, there is an identified urgent need for evidence based alternatives to pharmacotherapy for the treatment of anxiety that are feasible, potentially scalable, and can be delivered at the primary care and community levels [23, 24].

Mindfulness-based interventions (MBIs) in the treatment of anxiety, depression, or anxiety comorbid with depression are an emerging area of research interest [25–29]. MBIs offer a guided non-judgemental approach to attending to one’s lived experiences through techniques such as meditation and psychoeducation [30–32]. Other techniques include cultivating a focus on the present moment with self-compassion [30–32]. Emotion-focused mindfulness therapy (EFMT) is a MBI that emphasizes meditation, and observing thoughts and emotions as they arise [28]. EFMT has been demonstrated to reduce symptoms of anxiety in general populations [33, 34]. EFMT’s focus on meditation and the felt sense of emotions, rather than learning new material, makes it a promising intervention for reducing symptoms of anxiety for older adults who often report normal aging problems such as general forgetfulness and difficulty with word recall [8]. EFMT has not yet been tested in older adults or community dwelling adults with anxiety. It is hypothesized that EFMT will be feasible for community dwelling older adults who experience anxiety.

## Methods

### Participants, interventions, and outcomes

This study aims to evaluate the feasibility of EFMT for community dwelling adults 55 and older with symptoms of anxiety. The secondary outcomes will be measurements of changes to anxiety, sleep, and subjective memory functioning over time.

### Objectives

Primary objectives are as follows:
Determine if participants can be recruited, enrolled, and retainedDetermine if participants can adhere to all components of the intervention

Secondary objectives are as follows:
Examine the extent to which participants who receive the intervention have decreased levels of anxiety compared to those who do not receive the interventionExamine the extent to which participants have improved sleep quality compared to those who do not receive the interventionExamine the extent to which participants who receive the intervention have improved subjective memory functioning compared to those who do not receive the intervention

### Design and setting

The study is a feasibility randomized controlled trial (RCT) using a wait list control trial design. Due to COVID-19 restrictions, this study has been adapted from in-person delivery to telehealth delivery via Zoom. The first 48 people to meet the eligibility criteria will be randomly allocated to receive EFMT immediately, or in 8 weeks from time of baseline assessment (1:1 allocation ratio). Data will be collected by a blinded to group research assistant (RA) at baseline (T1), 8 weeks following baseline (T2), and 16 weeks following baseline (T3). Participants will be recruited from primary care clinics and community organizations that provide support to older adults. The principal investigator (PI)/facilitator of the EFMT groups will be blinded to the results of outcome assessments until the end of the intervention phase of the study. The PI is a registered psychotherapist certified in delivering EFMT and will facilitate all groups.

### Eligibility criteria

The PI will screen potential participants for the following inclusion criteria: participants will be community dwelling older adults 55 years of age and older with no existing therapeutic alliance with the PI; will self-report or have a diagnosis of anxiety; can speak English; and can commit to the 8-week program and three assessment phone calls with the RA. The presence of symptoms of anxiety will be assessed using the Geriatric Anxiety Inventory (GAI) with a cut off score of 10 which indicates the presence of anxiety [35]. Exclusion criteria will be having begun or stopped psychotropic medications within the previous six weeks [36]. Further exclusion criteria will be a Telephone Montreal Cognitive Assessment (T-MoCA) with a cut off score of 19 which indicates the possibility of mild cognitive impairment and would be beyond the scope of this study [37, 38]. The T-MoCA is conducted by telephone and, due to COVID-19 restrictions, will be administered by the PI by telephone, who has been certified in the administration and scoring of the MoCA. Potential participants will be considered eligible to participate in the study if: their GAI score is ≤ 10; and their T-MoCA score is ≤ 19 [37, 38]. The T-MoCA is conducted by telephone and is a validated version of the MoCA that assesses phonemic fluency; word recall and orientation to day, date, and location; and does not use items that require paper and pencil or animal identification [38, 39]. The T-MoCA is demonstrated to be accurate in detecting mild cognitive impairment (95% confidence interval) with excellent test-retest reliability and internal consistency [38, 39].

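### The score-based eligibility rule (GAI ≤ 10 and T-MoCA ≤ 19) contradicts the meaning the same section gives to both cut-offs

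*Protocol article*

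**What the plan says.** The section on participants, interventions and outcomes gives the aim as to "evaluate the feasibility of EFMT for community dwelling adults 55 and older with symptoms of anxiety".

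The Eligibility criteria section then makes three statements about the two screening scores:

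- Anxiety symptoms are assessed, among the inclusion criteria, by the "Geriatric Anxiety Inventory (GAI) with a cut off score of 10 which indicates the presence of anxiety".
- The T-MoCA appears under the exclusion criteria, "with a cut off score of 19 which indicates the possibility of mild cognitive impairment and would be beyond the scope of this study".
- The decision rule reads "Potential participants will be considered eligible to participate in the study if: their GAI score is" ≤ 10, "and their T-MoCA score is" ≤ 19.

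The section also lists criteria that do not depend on these scores. Among them is that anxiety be either self-reported or diagnosed. No other section restates or corrects the numerical rule.

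**The concern.** The third statement is the only place where the article turns the two cut-offs into a decision. If a GAI score of 10 signals the condition under study, eligibility should lie on the anxious side of it. If a T-MoCA score of 19 signals a condition outside the study's scope, eligibility should lie on the unimpaired side. The rule as written takes the other side both times.

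The rule affects the primary outcomes as well as the description of the sample. The first 48 people who meet the criteria are randomised (Design and setting). Feasibility of recruitment is judged by whether 70% of eligible people consent and whether 48 are enrolled in three months (Outcome collection and measures; Feasibility and acceptability outcomes). The GAI is also the anxiety outcome at all three timepoints, so an upper limit on it at screening carries into the secondary analysis. The Discussion says that the findings will inform recruitment time and sample size for a definitive trial. Those figures would come from a population other than the one named.

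**Working it through.** There is no stated figure to reproduce, so the check is one of logic. The sample size is internally consistent (4 blocks × 12 = 48, or 24 per arm) and does not bear on the point.

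**Inputs**, all from the Eligibility criteria section. Write g for the GAI score and t for the T-MoCA score.

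- Written rule: g ≤ 10 and t ≤ 19.
- Population that the cut-offs define: on the anxiety side of 10 and outside the possible-impairment side of 19.
- Assumption: higher g means more anxiety and lower t means worse cognition. The article does not state either direction.

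**Step 1, GAI alone.** The section does not say whether exactly 10 counts as anxiety, so take both readings.

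- Anxiety is g ≥ 10: with g ≤ 10, only g = 10 remains.
- Anxiety is g > 10: with g ≤ 10, nothing remains.

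**Step 2, T-MoCA alone.** Likewise for exactly 19.

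- Unimpaired is t > 19: with t ≤ 19, nothing remains.
- Unimpaired is t ≥ 19: with t ≤ 19, only t = 19 remains.

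**Step 3, both together.**

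| Reading of the cut-offs | Score pairs also allowed by the written rule |
|---|---|
| g ≥ 10 and t > 19 | none |
| g > 10 and t > 19 | none |
| g > 10 and t ≥ 19 | none |
| g ≥ 10 and t ≥ 19 | (10, 19) only |

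The overlap is empty in three of the four readings and a single pair in the fourth. An enumeration of integer score pairs gave the same result. It does not depend on the scale ranges, which the article does not give. Steps 1 and 2 also show that each inequality fails by itself, so correcting one would leave the other wrong.

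**Step 4, dependence on scale direction.** To defend both inequalities, a reader would have to reverse the ordinary direction of both instruments. Even then, if a T-MoCA score of 19 itself indicates possible impairment, that score is both excluded and eligible, whichever way the scale runs.

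**Step 5, what the denominator decides.** With 48 enrolled, the 70% criterion is met with 68 eligible people (48/68 = 70.6%) and missed with 69 (48/69 = 69.6%). The rule decides who is counted among those 68. The article gives no score distribution for applicants, so the size of any shift in the consent rate or the recruitment rate cannot be calculated.

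**The case against.** The best defence is that this is an error of notation. The section makes the purpose of both cut-offs plain, the principal investigator does the screening, and nothing shows that the reversed rule was ever applied. A symbol altered in typesetting or text conversion cannot be fully excluded. All of this stands. It bears on how the error arose and how likely it is to have done harm. It does not remove the contradiction, since both signs appear as ≤ and nothing elsewhere corrects them.

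Several stronger readings are tempting, and the article does not support them:

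- *The trial would enrol people without anxiety.* The self-report or diagnosis criterion applies whatever the GAI score. Those admitted would score at or below the GAI cut-off, which is different from being free of anxiety.
- *Everyone with low scores on both instruments would be accepted.* Meeting both score conditions is necessary but not sufficient. Age, residence, language, commitment to the programme, no existing therapeutic alliance with the investigator and no recent change in psychotropic medication also apply.
- *The rule shuts out the whole target population.* The aim names "community dwelling adults 55 and older with symptoms of anxiety" and sets no GAI threshold, so a person with diagnosed anxiety and a score below 10 could fit it. The near-empty overlap is with the population that the cut-offs define.
- *The GAI could not improve.* Scores from 1 to 10 can still fall. The GAI is also a secondary outcome for which the study is expressly not powered.
- *Other trial documents carry the same error.* The screening form, registry entry and ethics submission are not shown, so nothing can be alleged about them.

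**Conclusion.** The contradiction is real and must be corrected, because it lies in the rule that decides who is randomised. On the ordinary scale directions, the rule refuses everyone above the GAI cut-off and everyone above the T-MoCA cut-off. Among people who meet the remaining criteria, it admits those at or below the GAI cut-off who may have cognitive impairment. Its overlap with the population defined by the cut-offs is at most the pair (10, 19).

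The conclusion rests on two assumptions: the scale directions, which are inferred, and the signs being as printed. It does not rest on, or show, any misapplication in practice. If the rule were followed literally, the consent denominator and the recruitment rate would describe the wrong group, and baseline GAI scores would leave limited room for improvement. If it was not followed, the published rule still misreports who was eligible, and a reader who copied it would recruit a different population.

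**What to change.** Reconcile the eligibility sentence with the purpose that the same section gives to the two cut-offs; as written, both inequalities run against it. State whether a GAI of exactly 10 and a T-MoCA of exactly 19 qualify, and state the direction of each scale so that the rule can be read without outside knowledge.

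Confirm that the rule actually used in screening matches the corrected text. For enrolled participants this means checking their recorded screening scores. For people already refused it may have to rest on the recorded reason, because the Consent section has the data of ineligible applicants destroyed and only the reason for ineligibility noted. If any were screened under the reversed rule, report how many, since they affect the 70% criterion.

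The cost is a text correction and a review of screening records. No participants, visits or assessments are added.

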### Interventions

#### Comparators

The comparator will be no treatment (treatment as usual) for the controlled wait list group. All participants will receive the intervention. All participants will receive T1, T2, and T3 assessments within 7–10 days of each timepoint.

#### Intervention description

EFMT is a group intervention traditionally consisting of eight weekly in-person group meetings of 2.5 h, with group sizes of between 10 and 12 participants. Due to COVID-19 restrictions, EFMT will be delivered by Zoom to groups of six participants and weekly meetings will be shortened to 1.5 h to reduce Zoom fatigue, a phenomenon noted in popular media [40, 41]. For modification to video-delivery of the intervention, the number of participants has been decreased from 10 to 12, to six to provide adequate time for all components of the intervention to be delivered. Each group meeting consists of a check-in period of 5 min, the reading of meditation instructions by the PI, 20 min of silent unguided meditation, 5–10 min of journaling about what arose for participants during the meditation, and a 5-min break. After journaling, each participant takes a turn and describes their meditation experience, with the PI offering empathic exploration. In emotion-focused mindfulness therapy, as in emotion-focused therapy, empathic exploration is a core competency that involves reflection, validation, responding to participants, and heightening their emotional experience [42, 43]. This is the process that is the heart of change and encourages participants to become more familiar with, and develop a tolerance to, distressing emotions [33].

EFMT poses little risk for participants. Meditation can sometimes cause uncomfortable feelings to arise when participants connect with emotions. Participants may decide to withdraw from the intervention if overwhelming emotions emerge. Participants may decline to answer questions during the reporting part of the meditation group. Should a participant become upset during any part of the group, the PI can: ask that participant to remain after the group to talk; ask that group participants take a short break while the PI speaks with the upset participant; lead the upset participant through a relaxation and grounding exercise; ask the participant if the PI may contact someone of their choice for support; and help the upset participant to access counseling. Participants may withdraw from the study at any time; however, study participants will be retained in the trial wherever possible to enable follow-up data collection and prevent missing data.

### Outcome collection and measures

*Aim 1*. Determine if participants can be recruited, enrolled and retained

Recruitment, enrollment and retention data will be used to evaluate feasibility. Data will be gathered and measured on the number of potential participants referred and screened for eligibility, participants meeting eligibility requirements, participants enrolled, and participants completing the intervention. Recruitment and enrollment will be considered feasible if 70% of the total number of potential participants meeting eligibility requirements consent to enroll [44], and if 48 participants can be enrolled within a 3-month period (16 participants recruited per month). Retention will be considered feasible if 65% of participants complete data collection at both timepoints [45].Variables such as changes to medications, beginning, or stopping mental health counseling and significant life events will be tracked by the RA at T3 data collection timepoint. Extraneous variables will be important to gather to identify other potential reasons for changes to secondary outcomes aside from EFMT.

*Aim 2*. To determine if participants can adhere to all components of the intervention

Adherence will be used to measure acceptability. The intervention will be considered acceptable if 70% of participants attend of a minimum of six meetings [44]. As well, acceptability for measures of adherence to meditation, journaling, and reporting will be gathered through PI observation and documentation. Adherence to these components will be considered acceptable if the majority (75% or more) of participants appear to be meditating, journaling and actively report their meditations. Participants will not be required to practice between meetings; however, data will be gathered on the frequency and duration of home practice meditation and journaling to explore whether there is a relationship to outcomes. Participants will complete weekly reporting forms to be emailed to the PI. The PI will keep an observational diary noting what works well and perceived areas of challenge.

*Aim 3*. To determine the secondary objective of whether participants who receive the intervention potentially have decreased levels of anxiety compared to those participants who do not receive the intervention, the GAI will be used [35]. Outcome measures will be collected using the GAI at T1, T2 and T3.

To determine the secondary objectives, the extent to which participants who receive the intervention potentially experience changes to sleep quality and subjective memory functioning compared to participants who do not receive the intervention, the Pittsburgh Sleep Quality Index (PQSI) and the Multifactorial Memory Questionnaire (MMQ) will be used [46, 47] (Fig. 1).

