### Feasibility and acceptability outcomes

Feasibility and acceptability outcomes will be determined by the following: recruitment and enrollment will be considered feasible if 70% of the total number of potential participants meeting eligibility requirements consent to enroll [44], and if 48 participants can be enrolled within a 3-month period (16 participants recruited per month). As a dropout rate of 35% is consistent with MBIs based in self-management and with a technology based delivery, a retention rate of 65% will be used to determine feasibility [65, 66]. Participants’ adherence to all components of the intervention will be defined by attendance of 6/8 sessions and participation in meditation, journaling, and reporting during the sessions, as observed and documented by the PI. In the tradition of MBI research, the intervention will be considered complete if participants are able to attend a minimum of 6/8 meetings [45]. It will be assumed that participants will be honest about meditation within the group, although direct evidence can only be inferred through observation [67]. Participants are not required to practice at home; however, they will be asked to self-report on the frequency and duration of home practice meditation and journaling to explore whether there is a relationship to outcomes.

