### Consent

Prior to screening for eligibility, each potential participant will receive an emailed copy of the Letter of Information/Informed Consent and will provide informed consent to the PI at the beginning of the screening call (Additional file 1). Data gathered from screened potential participants not eligible to participate will be destroyed. The reason for ineligibility will be noted. All data will be anonymized. In the event of withdrawal from the study, the participant will have the choice of requesting that collected data be destroyed or to give consent to include data for analysis.

The purpose of this protocol is to ensure transparency and reproducibility of the results of this study. Therefore, this protocol will be available publicly through journals and trial registries [66, 71]. The deidentified data will be archived to Queen’s University Scholars Portal Dataverse, a repository for research data that is stored on Canadian servers in a secure environment, within 3 years of collection and will be available for sharing [72].

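### The 70% consent limb of the recruitment criterion says almost nothing about uptake, because consent is taken before eligibility is known

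*Protocol article*

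**What the plan says.** Two sections of the protocol article set the same threshold. Under Outcome collection and measures (Aim 1): "Recruitment and enrollment will be considered feasible if 70% of the total number of potential participants meeting eligibility requirements consent to enroll". Feasibility and acceptability outcomes repeats it. Both sections join it to a second requirement, 48 participants enrolled within 3 months at 16 per month.

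The Consent section fixes the order of events: "Prior to screening for eligibility, each potential participant will receive an emailed copy of the Letter of Information/Informed Consent", and that person "will provide informed consent to the PI at the beginning of the screening call". No later consent is described.

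Eligibility criteria lists among the inclusion criteria that the person "can commit to the 8-week program and three assessment phone calls with the RA".

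Design and setting adds: "The first 48 people to meet the eligibility criteria will be randomly allocated".

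The counts to be kept under Aim 1 are people referred and screened, people eligible, people enrolled and people completing. Refusals are not listed.

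**The concern.** An uptake rate is informative only if the people in its denominator still have the chance to say no. Here the denominator is formed after consent has been given. Someone who refuses at the start of the call is never screened and cannot be counted as eligible. Someone who consents but will not commit is classed as ineligible and also leaves the denominator. Both kinds of unwillingness disappear from the rate.

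Recruitment and enrolment belong to the primary objectives. Sample size justification says the study should show whether a large study is warranted, and the Discussion says it will inform the recruitment time of a definitive trial. A reader who sees the 70% benchmark passed would take it as evidence that eligible older adults accept the programme, when it may reflect only the order of the procedures.

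**Working it through.** **1. The plan's own figure.** 16 per month × 3 months = 48. This agrees with Sample size justification: 4 blocks × 12 = 48, or 24 per arm. The 70% is a threshold taken from a cited source, so there is no derivation to reproduce.

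**2. The rate under the stated order.** Let R be the people approached, c the fraction who consent at the start of the call, and e the fraction of consenters found eligible. The article gives none of these, so the values below are assumed.

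Eligible = R × c × e. All of them have consented, so consent among the eligible = (R × c × e) / (R × c × e) = 1.

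| R | c | e | Eligible | Consent among eligible |
|---|---|---|---|---|
| 100 | 30% | 60% | 18 | 100% |
| 200 | 50% | 40% | 40 | 100% |
| 300 | 20% | 80% | 48 | 100% |
| 150 | 90% | 60% | 81 | 100% |

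Willingness among those approached runs from 20% to 90%, and the rate does not move.

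**3. Effect of the commitment criterion.** Suppose 69 people meet the GAI, T-MoCA and medication criteria and 21 of them are unwilling to commit (assumed). Classed as ineligible, they leave 48/48 = 100%. Classed as decliners, they give 48/69 = 69.6%. The same behaviour passes or fails the 70% bar according to that label.

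**4. The looser reading, enrolled over eligible.** With 48 enrolled, the bar is crossed at 48/0.70 = 68.57 eligible:
- 68 eligible: 48/68 = 70.6%, pass
- 69 eligible: 48/69 = 69.6%, fail

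So 69 − 48 = 21 people who had already consented and been found eligible would have to be lost before enrolment.

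**5. Can that looser rate discriminate?** Binomial chance of reaching at least 70%, for an assumed true probability that an eligible person enrols:

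| Eligible (number needed) | 90% | 80% | 70% | 60% |
|---|---|---|---|---|
| 48 (34) | 1.00 | 0.96 | 0.52 | 0.08 |
| 60 (42) | 1.00 | 0.98 | 0.56 | 0.07 |
| 69 (49) | 1.00 | 0.97 | 0.49 | 0.04 |

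It can. A 70% threshold separates 80% from 60% well, provided there is a real decision between eligibility and enrolment. The weakness lies in where the criterion is applied and not in the number 70.

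**The case against.** The case against is that the article treats enrolment as its own event. Eligible and enrolled are counted separately under Aim 1, Recruitment collects characteristics at the time of enrolment, and Randomization speaks of people the investigator has enrolled. Two counts make sense only if an eligible person may fail to enrol. The consent form is an additional file that is not shown and may be two-stage, and a condensed article may have dropped the step. All of this stands, and it means a rate below 100% cannot be ruled out. It does not remove the conflict: the one consent described comes before eligibility, while the criterion counts consent among the eligible.

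Three stronger conclusions are tempting, and the document does not support them.

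- *The criterion cannot fail.* This is strictly true only if consent means the consent given at the start of the call. On the enrolled-over-eligible reading it can fail. The statement that the first 48 eligible people are randomised does not settle the matter, since the target elsewhere is 48 enrolled, with no cap on how many may be eligible.
- *The recruitment outcome is met automatically.* It is not. Low uptake slows accrual and can fail the 48-in-3-months limb. That limb measures speed, however, and can be met at low acceptance if enough people are approached.
- *The definitive trial learns nothing about yield.* Referred and screened counts are kept, recruitment and enrolment rates are to be calculated, and Consent says reasons for ineligibility are noted, so people excluded for not committing may be identifiable. What is missing is a listed count of refusals and a threshold that uses it.

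The commitment criterion may also be meant as availability and not willingness. The article does not say which.

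**Conclusion.** The concern holds for one limb of a two-part primary criterion. Under the order stated in the article, consent among eligible people is about 100% whatever the willingness of those approached, so the 70% threshold is close to uninformative about uptake. With 48 enrolled, it could be missed only on the enrolled-over-eligible reading and only with at least 21 of 69 consented, eligible people lost before enrolment.

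This rests on two assumptions: that the start-of-call consent is the only one, as the article describes, and that people unwilling to commit are recorded as ineligible. If the consent form has a second decision after screening, the rate is meaningful and the repair is mainly to say so.

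This is more than a wording matter, because it determines what a primary feasibility criterion can conclude. It is also confined: the accrual limb and the recruitment counts still work as intended.

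**What to change.** Reconcile Outcome collection and measures, Feasibility and acceptability outcomes, and Consent in one of two ways.

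- **(a) Two decisions.** Treat the start-of-call consent as consent to screening. After eligibility is confirmed, record a yes/no decision to enrol and compute the 70% on it. Count people who meet the GAI, T-MoCA and medication criteria but are unwilling to commit as decliners, in the denominator and not the numerator.
- **(b) Single-stage consent.** Apply the criterion to people approached or sent the information letter, and log refusals. The letter is the easier count, because advertising on a website and social media gives no number reached. The 70% would need fresh justification, since it was set for a different denominator.

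Option (a) keeps the threshold and its meaning. In either case, report the proportion of people sent the letter who agreed to screening.

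The cost is a slightly longer screening log and possibly an amendment to the consent wording. Reported uptake is likely to look less favourable. The change should be made before recruitment starts, because refusals that are not logged at the time may not be recoverable and data on ineligible people are to be destroyed.
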